### Data collection

The testing procedure will occur at one primary care rehabilitation site and participants will be tested by physical therapists at baseline (pre-training) and at post training. Data collection will be comprised of both clinical performance tests of gait (single and dual-task), functional strength and mobility (single and dual-task), balance, cognition as well as self-reported questionnaires. All participants will be tested during the ON-phase of their medication (approx. 1–2 h following intake of anti-Parkinson medication) and testing will be scheduled to occur at the same time on both test occasions. During assessments of gait and functional mobility, participants will wear six inertial sensors (Opal, APDM Inc.) placed on feet, wrists, lumbar and sternum, to capture various spatiotemporal gait parameters.

### Primary outcome measure

The six-minute walk test (6MWT) is the primary outcome measure to assess efficacy of the intervention to improve walking capacity in PD. This test of walking capacity is reliable and valid for use in older adults and in PD [35, 36]. Participants are instructed to cover as much distance as possible, by walking back and forth between two cones placed 30 m apart, during a 6 minute interval. Participants will rate their perceived exertion and level of breathlessness using the Borg RPE and Borg CR-10 scales respectively, before and after the test [37]. When compared to healthy controls of similar age, people with PD walk at lower gait speed and with shorter stride lengths during the six-minute walk [38]. The distance covered during this test is also related to PD motor features such as bradykinesia and impaired balance [39].

### Secondary outcome measures

Gait performance during single and dual task conditions will be assessed with the 2-minute walk test (2MWT), a valid test of gait endurance in PD [40]. The single task 2MWT will be performed 10 min after completion of the 6MWT. The 2MWT will thereafter also be performed in a dual task condition during which a cognitive task, the auditory Stroop task, will be performed simultaneously while walking. During this task participants will be presented with the Swedish words for “high” and “low” in congruent (25% of stimuli) and incongruent (75% of stimuli) high and low tones via wireless headphones (Razer Thresher Ultimate). Participants will be instructed to respond verbally to the corresponding tone as quickly and correctly as possible. Verbal responses will be recorded using Audacity (version 3.2) to evaluate accuracy and reaction times. The auditory Stroop task will also be performed in a seated position in order to capture single task performance.

Gait speed will further be captured using the 10-meter Walk Test – a clinically feasible test of gait speed with proven reliability and validity in PD [41]. Participants will perform the test under two conditions, whereby they will walk a 14-meter walkway at their self-self-selected ‘usual’ gait speed and during fast walking. Testing the repeated ability to perform sit-to-stand is an easily administered clinical test which measures lower limb functional strength [42]. The five times sit-to-stand test (5TSTS) is a recommended version of this test [43], which has been reliability tested in PD cohorts and test scores also strongly relate to balance and bradykinesia in PD [44]. Functional mobility will be measured using the Timed Up and Go test [45], during both single (TUG test) and dual-task conditions (Cognitive TUG). Changes in both the amount and the intensity of physical activity behavior will be captured using the ActiGraph accelerometer model GT3X+ (Acti-Graph, Pensacola, FL, US), worn at the waist. Total daily step counts, as well as time spent (absolute and relative values) in different physical activity intensities – Sedentary behavior; Light intensity physical activity and Moderate-vigorous intensity physical activity – will be evaluated. Participants are asked to wear the accelerometer for seven consecutive days and the device will be set to sampling counts of 1-minute epochs. ActiLife software (Acti-Graph, Pensacola, FL, US) will be used to extract and process this data. Physical activity behavior will be captured at a third time interval, approximately one-year post-intervention to account for seasonal differences in weather changes as well as the achievement of long-term PA goals. Balance performance will be assessed using the 14-item Mini Balance Evaluation Systems test (Mini-BESTest) [46].

A variety of patient reported outcome measures will be assessed at both time intervals. Self-rated health and quality of life will be measured using the generic EuroQol EQ- 5D [47] and the disease-specific Parkinson’s Disease Questionnaire (PDQ-39) [48]. The EQ-5D is a non-disease-specific standardized assessment of health-related quality of life, which is widely implemented in Swedish healthcare. Respondents are required to rate their health status in relation to five dimensions; mobility, self-care, usual activities, pain/discomfort, and anxiety/depression. Self-perceived walking ability during 12 different everyday-life situations will be rated using the Swedish version of the Walking impact scale (walk 12G) [49] and participants’ balance confidence during a range of potentially challenging activities will be captured using the Activities-specific balance confidence (ABC) scale [50]. Participants’ perceived confidence, or self-efficacy to perform physical activity and exercise will be measured with the Swedish version of the exercise self-efficacy scale (S-ESS), which is reliable for use among people with neurological disease [51]. Depression and anxiety will be assessed using the Hospital Depression and Anxiety scale (HADS), which consists of two sub-scales, each incorporating 8 questions [52]. Participants will be asked to fill out all questionnaires at home. The System Usability Scale will be used to evaluate the demand and usability of the eHealth tool, [53] and perceptions of the home training programs will be investigated in both groups via a questionnaire after the 10-week period.

The Montreal Cognitive assessment (MoCA), which has good psychometric properties regarding global cognition in PD [54] will be used as a screening test for eligibility for inclusion to the study. Executive function will be assessed using Trail Making Test (TMT) II and IV from Delis Kaplan Executive Function System (D-KEFS).

### Adherence

Both intervention and control group participants will receive a home exercise diary at study outset where they note each completed training session. In addition, participants in the intervention group will also rate their level of exertion using the Borg RPE scale following each exercise session in the application. The intervention group will also note the number of steps taken each day during the 10-week period, in line with the goal of engaging in 60 min of walking per week.

### Intervention

The two training regimens in the STEPS trial will occur over a 10-week period but differ regarding intervention-targeted behavior, cognitive-behavioral elements, and dose. For an overview of respective group regimen, see Table 2.

### Intervention group condition

Participants in the intervention group will perform exercise guided by videos in a mobile application, viewed on a digital tablet three times per week. Baseline assessment will determine the level of motor difficulty (three levels) and cognitive dual task difficulty (two levels) that each participant will be assigned to. Assignment to level of motor difficulty will be decided on a case-to-case basis by the research team and be guided by participants baseline performance and (1) self-reported ability to transfer from floor to chair, (2) balance performance using the Mini-BESTest, and (3) usual gait speed measured during the 6MWT. Assignment to the level of difficulty of the cognitive dual tasks will be guided by (1) global cognition using the MoCA, and (2) performance (completion time, safety during transfers and turning, and performance on the serial subtraction task) during the TUG cog. The initially assigned levels of motor/ cognitive challenge can be altered during the training period if deemed appropriate.

Following randomization, a researcher not involved in assessments will perform a home visit or digital visit among participants to establish the safety of the home exercise environment. Short- and long-term goals regarding increasing physical activity behavior will be discussed, decided and documented during the home/digital visit. Progress towards attainment of the short-term goals will be followed up mid-intervention (5 weeks) and post-intervention (11 weeks). Commercial waist-worn pedometers (Rubicson) will be distributed for participants to track physical activity behavior (steps per day) during the intervention period. Long term physical activity goals and objective physical activity behavior will be assessed one year post intervention. The process of designing behavioral change components of the intervention was guided by an evidence-based behavioral change framework characterizing essential components of behavioral change [55] and involved elements such as, education, goal setting, goal reflection, self-monitoring and reflection, as well as digital support.

All training sessions will include the components, warm-up, functional strength exercises, cardiovascular exercises, and cool-down. As of week three, the first and last session each week will also include motor-cognitive dual task elements. Figure 1 illustrates the user view of a single dual-task exercise. A schematic overview of the different types of dual-task exercises, and time spent in them can be seen in Additional file 1. The cognitive tasks were selected to specifically target the neurocognitive domains, selective attention, working memory, recognition of emotions and verbal fluency (See Additional file 2 for examples of exercise instructions, progression, and display features). During the first five weeks of the training period, weekly support will be provided using the chat function on the mobile application or via telephone, and additional support provided when needed.

**Fig. 1 Fig1:**
[figure not shown]
User view of a motor-cognitive exercise involving counting categories (happy blue faces) appearing on the screen (top left). The light bulb icon (bottom left) indicates the dual-task nature of the exercise, which lasts for 45 s (countdown bottom right)

**Table 2 Tab2:** Description of intervention and control group regimen

	Intervention group	Control group
**Delivery mode**	Exercise Application	Paper handout
**Individual adaptation**		
* To level of motor function*	Yes	Yes
* To level of cognitive function*	Yes	No
**Exercise dose**		
* Home training sessions / week*	3	3
* Walking*	Min. 60 min / week	No
* Training period*	10 weeks	10 weeks
**Exercise progression**	Inbuilt, supported	Optional, unsupported
**Core components**		
Motor/ motor-cognitive elements:		
* Functional strength*	Yes	Yes
* Flexibility*	Yes	Yes
* Cardiovascular*	Yes	No
* Cognitive dual tasks*	Yes	No
Cognitive-behavioral components:		
* Short & long-term PA goal setting*	Yes	No
* Self-monitoring and reflection*	Yes	No
* Educational/motivational videos*	Yes	No
* Remote support* via video / phone	Yes	No

### Control group condition

Participants in the control group will receive a paper printout with home exercises to be performed three times per week. The home exercise program will be instructed by a physiotherapist at an in-person visit scheduled after baseline assessments. Level of motor difficulty (three levels) will be decided by the same criteria as in the intervention group. The exercises will focus on functional strength, flexibility, and balance. Written information on how exercises can be progressed will be included, but no support for progression will be given during the training period. Should participants in the active control group have further questions or concerns regarding their exercise program, they will be able to contact their physical therapist by telephone.

### Power and sample size estimate

A sample size calculation was conducted to determine the number of participants needed to evaluate an ‘intervention group’ compared to an ‘active control group’. A previous study investigating functional limitations and task performance among people with mild and moderate Parkinson disease has reported 6MWT performance of 460.24 ± 107.09 and 397.81 ± 104.02 (mean ± standard deviation) [56].

Assuming a mean and standard deviation of 460.24 and 107.09 m respectively, the study would require a sample size of: 58 participants for each group (a total sample size of 116, assuming equal group sizes), to achieve a power of 80% and a level of significance of 5% (one sided), for detecting an intervention effect (difference between treatments) in means between the intervention and the control group of 50 m. Considering a 5% drop-out, the study would require a sample size of: 60 participants in each group (a total sample size of 120). The calculations were done using a two sample mean test, one sided test, in STATA version 17.

### Statistical analysis plan

Analysis will be performed based on intention to treat and per protocol basis. The two-sided 0.05 level will be applied for significance in all analyses, except the main outcome 6-minute walk test, which is tested with a one-sided test.

Baseline demographics and other patient’s characteristics will be tabulated and summarized by treatment group. Continuous variables will be described by standard descriptive statistics (mean, standard deviation, median, interquartile range, minimum, and maximum), and categorical variables will be summarized by frequency tables with number and proportion in each category (with the corresponding sample sizes).

In the primary analysis of the effect of STEPS intervention to improve walking capacity in comparison to the active control condition a linear mixed model (LMM) with subject-specific random intercept will be specified to assess possibles changes in 6MWT performance over time within and among groups. LMM accounts for both fixed and random effects, can analyze data with repeated measures as well as can handle missing values. Specifically, the LMM will include treatment, time, levodopa equivalent dose and time*treatment interaction term as fixed effects, and subject/participant as a random effect. An unstructured correlation matrix will be used. Missing values will be imputed as part of the LMM model assumptions. A linear regression model will be adjusted for studying the influence of baseline demographics, patient’s medical history variables and treatments on the change in 6MWT performance.

In terms of the secondary outcomes, for continuous variables, linear mixed models (LMM) with subject-specific random intercept will be specified to assess possibles changes over time within and among the intervention and control groups. The strength of the effect size will be calculated using Cohen’s d for all outcomes that are normally distributed. For dichotomous variables, change in proportions within groups at end of treatment with respect to baseline (pre-treatment vs. post-treatment) will be assessed using McNemar’s test. For categorical variables, frequency distributions will be estimated and compared between the groups using Chi-squared test or the exact Fisher test.

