### Screening and recruitment

Participants will be recruited using a varied approach through advertisement in patient organization publications, by distributing ethically approved study flyers to neurologists/ rehabilitation practitioners and by advertisement on social media platforms managed by the responsible academic (Karolinska Institutet) and clinical sites (Primary Care Rehabilitation at Stockholm Sjukhem, Sweden). The recruitment process will occur systematically in the following sequence: Potential participants who have registered interest in the study will be contacted by study coordinators for an initial telephone interview. After the telephone screening, eligibility of potential participants will be established at an in-person clinical assessment. Prior to the assessment, potential participants will receive verbal and written information of study procedures and be given the chance to pose questions. Recruitment will occur in three to four successive waves, consisting of 30–40 participants per wave. Participants will be randomly assigned in a 1:1 ratio to the intervention or control groups. Participants in both groups will be encouraged to continue their usual daily activities during the 10-week period between measurements. They will however be advised against participating in parallel research studies aiming to affect health or adjusting their PD medication during the 10-week period.

**Table 1 Tab1:** Inclusion and exclusion criteria

Inclusion criteria	Exclusion criteria
Idiopathic Parkinson’s disease	No internet connection in the home
Hoehn & Yahr stage 1 - 3	Pre-existing orthopedic or neurological diseases affecting gait
Montreal Cognitive Assessment score ≥ 21 points	Visual or hearing impairments impeding intervention delivery
Age ≥ 50 years	≥ 2 falls one month prior to inclusion
Able to walk independently indoors for six minutes without a walking aid.	

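### The primary mixed model tests a plain difference in 6MWT change; adjusting for baseline 6MWT would gain precision at no cost, and the levodopa term as written does almost nothing

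*Protocol article*

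**What the plan says.** In the protocol article, the section Statistical analysis plan specifies for the primary outcome "a linear mixed model (LMM) with subject-specific random intercept will be specified to assess possibles changes in 6MWT performance over time", and then that "the LMM will include treatment, time, levodopa equivalent dose and time*treatment interaction term as fixed effects, and subject/participant as a random effect". It adds that "An unstructured correlation matrix will be used". A separate linear regression, aimed at "studying the influence of baseline demographics, patient" history and treatment, has the change in 6MWT as its outcome; baseline 6MWT is not named among its covariates.

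Under Data collection, "participants will be tested by physical therapists at baseline (pre-training) and at post training", so the 6MWT has two time points. Study design and setting places randomisation after the baseline assessment. Screening and recruitment says that participants will be advised against "adjusting their PD medication during the 10-week period". The text does not say whether the levodopa equivalent dose in the model is the baseline value or the value at each visit.

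**The concern.** Baseline 6MWT is measured before allocation, so the two arms have the same expected baseline. A model with a free treatment main effect does not use that fact. It lets the arms differ at baseline and compares their changes. Two things are at stake.

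- **Precision.** A difference in change has a larger variance than a baseline-adjusted comparison at any rho below 1. It also over-corrects a chance imbalance: an arm that happens to start high will on average show a smaller change.
- **The one named covariate.** Levodopa dose is there to adjust the comparison, but it enters as a main effect only. A value that is constant over time cancels from within-person change. A value that varies by visit is partly measured after randomisation. Neither form gives a clean and useful adjustment.

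**Working it through.** **Inputs.** From Power and sample size estimate: SD 107.09 m; a target difference "in means between the intervention and the control group of 50 m"; one-sided 5% level; 80% power; 58 per arm before and 60 per arm after 5% drop-out. Completers: 60 × 0.95 = 57 per arm, 114 in all. Not in the documents: rho, the correlation between baseline and post-training 6MWT, assumed here to lie between 0.3 and 0.9. Equal SDs at both visits are also assumed.

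**The plan's own figure.** The normal approximation gives 57 per arm; the exact one-sided two-sample t-test gives 58 (power 0.804). The stated 58 is reproduced. That calculation compares means at a single time point and makes no use of baseline.

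**What the model estimates.** Write D for post minus baseline.

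1. The mean model is a + b·arm + t·time + d·(arm × time) + c·dose. If dose is constant over time, the mean of D is t + d·arm: b and c drop out.
2. With complete data the likelihood splits into the distribution of D, which contains t and d, and the distribution of baseline given D, whose intercept, arm and dose coefficients are all free. The second part carries no information on d. So the estimate of d is the difference in mean D, with or without dose. This holds for a random intercept and for an unstructured matrix alike.
3. Participants with a baseline value only break the exact split, so dose then has a small influence.

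**Numerical check.** Two-visit data were simulated with 60 per arm and residual SD 107.09, one data set per setting, and the random-intercept model was fitted.

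- Complete data, rho 0.6: difference in change 52.9586; model without dose 52.9586 (SE 16.252); model with baseline dose 52.9586 (SE 16.252). Model with a visit-specific dose: 54.106.
- 5% of post values missing: adding baseline dose moved the estimate from 24.79 to 25.42 (rho 0.6), from 49.23 to 49.48 (rho 0.8) and from 45.97 to 45.98 (rho 0.9).

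**Variance.** Per arm and per participant, the change has variance 2·SD²·(1−rho), and the baseline-adjusted outcome has SD²·(1−rho²). The ratio of adjusted to change is (1−rho²) / [2(1−rho)] = (1+rho)/2. Power is for 50 m with 57 completers per arm, one-sided 5%.

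| rho (assumed) | SD of change, m | SD adjusted, m | Variance ratio | Power, change | Power, adjusted |
|---|---|---|---|---|---|
| 0.3 | 126.7 | 102.2 | 0.65 | 0.673 | 0.830 |
| 0.5 | 107.1 | 92.7 | 0.75 | 0.797 | 0.888 |
| 0.6 | 95.8 | 85.7 | 0.80 | 0.870 | 0.927 |
| 0.7 | 83.0 | 76.5 | 0.85 | 0.940 | 0.966 |
| 0.8 | 67.7 | 64.3 | 0.90 | 0.989 | 0.994 |
| 0.9 | 47.9 | 46.7 | 0.95 | about 1.00 | about 1.00 |

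In participants: 114 analysed with baseline adjustment carry the information of 114/0.75 = 152 analysed by change at rho 0.5, 114/0.85 = 134 at 0.7, 114/0.90 = 127 at 0.8 and 114/0.95 = 120 at 0.9.

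**Chance imbalance.** The standard error of the baseline difference at 60 per arm is 107.09 × √(2/60) = 19.6 m. Given a baseline difference B, the expected change-score estimate is off by (1−rho)·B in the opposite direction: 0.5 × 19.6 = 9.8 m at rho 0.5, and 0.2 × 19.6 = 3.9 m at rho 0.8. Baseline adjustment removes this shift.

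**The case against.** The strongest reply is that nothing here is invalid. The difference in change is unbiased over randomisation, it answers the stated hypothesis about improvement over 10 weeks, and a two-visit mixed model with treatment, time and their interaction is conventional. The over-correction is an error conditional on an observed imbalance, not a bias. The trial was sized on an unadjusted comparison, so at rho of 0.5 or more the stated model has essentially the planned 80% power or better, and at 0.8 or 0.9 the gain in power is negligible. All of this stands. It limits the size of the point but gives no reason to prefer the less precise estimator.

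A reader might also infer more than the documents support:

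- **That baseline 6MWT is thrown away.** It is not. It is subtracted, which cuts the analysed SD from 107.09 m to 67.7 m at rho 0.8. The change analysis does worse than ignoring baseline only if rho is below 0.5.
- **That the levodopa term never has any effect.** This is exact only with complete data. At the planned 5% drop-out its effect is small but not zero.
- **That the plan conditions on a post-randomisation dose.** The text does not say so. A condensed article may leave the timing to the full analysis plan, and the advice not to change medication limits the harm if a visit-specific dose were used.
- **That the regression on change must be replaced.** It is not the primary analysis, and its broad covariate groups do not rule out baseline 6MWT. Once baseline is in the model, the treatment coefficient is the same for change and for post value.
- **That the secondary mixed models share the fault.** Their fixed effects are not listed, so no defect is shown there.

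**Conclusion.** The point holds as a free improvement in precision, not as an error of validity. As specified, the primary test is a difference in mean change, exactly so with complete data and nearly so at 5% drop-out. Baseline adjustment would reduce the variance by 25% at rho 0.5, falling to 5% at rho 0.9. It would also remove a shift of 9.8 m (rho 0.5) or 3.9 m (rho 0.8) per one-standard-error baseline imbalance, against a 50 m target. These sizes rest on an assumed rho and on equal SDs at the two visits. The model's structure follows directly from the stated terms and needs neither assumption.

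The levodopa term, if it is the baseline dose, is harmless but does essentially nothing for the treatment effect. If it is a visit-specific dose, the effect is conditioned on a value recorded after randomisation. That second consequence is conditional on a choice the text leaves open. How much a properly entered baseline dose would add cannot be judged from the documents.

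**What to change.** Make the primary analysis baseline-adjusted, in one of two forms:

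- ANCOVA: regress post-training 6MWT on arm, baseline 6MWT and baseline levodopa equivalent dose; or
- a mixed model with a common baseline mean, that is, time, time-by-treatment, baseline levodopa dose and dose-by-time, with no treatment main effect. This form keeps participants who lack a post-training value in the model.

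State that the levodopa dose is the pre-randomisation value. In the separate regression on change, name baseline 6MWT as a covariate; the outcome can stay as change. Apply the same baseline adjustment to continuous secondary outcomes for which a baseline is collected.

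The cost is a change of wording, made before the allocation is unblinded. Baseline 6MWT is already measured and levodopa dose is already in the model, so only its timing needs fixing. No extra participants or visits are needed, and the sample size calculation can stay as it is.
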